| Outcome(s):                     | 
 
1. The first primary outcome will be the maintenance of HIV-RNA <100 copies/ml through the 48-week study duration.
 
2. Secondary outcomes will include the maintenance of HIV-RNA <50 copies/ml through 48 weeks of follow-up (classical proportion and by FDA snapshot), loss of future drug options, change in CD4 cell count, DTG and FTC plasma levels, safety, treatment satisfaction, monitoring satisfaction, health-related quality of life, study satisfaction, and costs. The second primary outcome will be to assess the direct costs of patient-centered monitoring.
 
 
Secondary outcomes will include acceptability, safety, satisfaction and cost-effectiveness of monitoring arms.
                                                                                                                                                                                                                                                                                                                                                                                                                                                                                                                                                            |

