| Statistical Considerations: | 
DTG + FTC dual therapy is expected to be non- inferior to standard-of-care using a 12% non-inferiority margin assuming that 92% of patients are virologically suppressed at week 48 in the two comparison arms.
 
We will evaluate the proportion of patients with viral suppression at week 48 in each arm, and compute a Mantel-Haenszel risk difference (DTG+FTC minus cART) stratified by monitoring type with a two-sided 95% confidence interval. If the lower confidence limit is higher than -12% we will conclude non-inferiority. If the lower confidence limit is below -12% we will conclude that DTG + FTC is potentially inferior to cART. Per protocol (PP) and intention-to-treat (ITT) analyses will be performed. Exclusion criteria for PP will be: patients who discontinue treatment prematurely for reasons other than death, patients with a treatment adherence of less than 80%, or those who do not have HIV-1 RNA results available at week 48. For ITT analysis, all randomized patients will be analysed in the allocated group regardless of any protocol violations.
 |
| GCP Statement:              | 
This study will be conducted in compliance with the protocol, the current version of the Declaration of Helsinki, the ICH-GCP or ISO EN 14155 (as far as applicable) as well as all national legal and regulatory requirements.
                                                                                                                                                                                                                                                                                                                                                                                                                                                                                                                                                                                                                                                                                                                                                                                                                                                                          |

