| Health related costs assessment                                                                                            |   |   |                                                                                     |     |     |     | X |

 Safety serum chemistry includes CK, creatinine, ASAT, ALAT, gamma-GT, alkaline phosphatases; glucose and lipid profile.

 Patients with HIV-RNA between 20 and 99 copies/ml will benefit from another HIV-RNA measurement after 6 weeks (± 5 days). Patients with HIV-RNA ≥ 100 copies/ml will benefit from another HIV-RNA measurement after 2 weeks (± 5 days).

\* CD4-count, full blood count and safety serum chemistry will be performed on a 3-monthly basis for patients randomized in the standard monitoring arm. Patients randomized in the patient-centered monitoring arm will benefit from these routine tests on a yearly basis (i.e. at day 0 and week 48).

\* Patients new to DTG will benefit from CK measurement and from hepatic safety serum tests, i.e. ASAT, ALAT, gamma-GT, alkaline phosphatases, at week 6 whatever monitoring arm.

† Diabetic patients under concomitant metformine and dolutegravir will benefit from blood glucose and creatinine measurements at weeks 6, 12, 24 and 36 whatever monitoring arm.

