### 3.7 Risks / Benefits

The main risk in this trial is virological failure on DTG + FTC dual therapy. In the ART Cohort Collaboration of 18 cohorts from Europe and North America including about 17900 patients, low level viremia measured between 50 and 199 copies/ml was weakly associated with virological failure (aHR 1.38, 95%CI 0.96-2.00) (85). We will measure HIV-1 RNA level in the plasma on a regular basis to monitor for low level viremia. Any patient with HIV-1 RNA  $\geq 100$  copies/ml will undergo an additional HIV-1 RNA measurement 14 days later ( $\pm 5$  days), as well as additional adherence session and review of concomitant medications and dolutegravir and emtricitabine plasma concentration measurements.

We will define virological failure as plasma HIV-1 RNA  $\geq 100$  copies/ml on two consecutive measurements. Any patient reaching virological failure will be assessed for genotypic resistance and pharmacogenetic analyses. This latest analysis will be only done in patients who are included in the SHCS and have also signed a consent form for genetic studies. In case of virological failure, the patient will undergo an additional medical visit with review of adherence, concomitant medications, discussion of results of DTG + FTC plasma concentration. Patients randomised in the DTG + FTC dual therapy arm will be switched to a standard cART regimen while waiting for results of genotypic resistance. Patients randomised in the continuing cART arm will await results of the genotypic results. In both cases, treatment will be adjusted according to genotypic resistance results. All failing patients will complete study procedures until week 48. Figure 3 presents the algorithm for the management of virological failure.

Any patient with HIV-RNA between 20 and 99 copies at any time of scheduled visits will have an additional HIV-RNA measurement after 6 weeks (+/-5 days).

Figure 3: Algorithm for the management of virological failure

[figure not shown]

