## 5. STUDY OUTCOMES

### 5.1 Primary Outcomes

The *first primary outcome* for the comparison between DTG + FTC dual therapy and standard cART is the proportion of patients maintaining HIV suppression defined as HIV-RNA <100 copies/ml throughout 48 weeks (+/- 21 days). A single blip defined as HIV-RNA <200 copies/ml during the study period is allowed as long as this value is followed by HIV-RNA <50 copies/ml.

The *second primary outcome* for the comparison between patient-centered and standard monitoring is the direct costs of the two study arms from the health care system perspective at week 48.

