### 5.2 Secondary Outcomes

1. Proportion of patients maintaining HIV suppression defined as HIV-RNA <50 copies/ml throughout 48 weeks (+/- 21 days). A single blip defined as HIV-RNA <200 copies/ml during the study period is allowed as long as this value is followed by HIV-RNA <50 copies/ml;
2. Proportion of patients with HIV-RNA < 50 cp/ml at week 48 by FDA snapshot analysis; Proportion of patients experiencing loss of future drug options defined as new intermediate or high-level resistance to one or more drugs to which the patient's virus was considered sensitive at trial entry;
3. Time to loss of virological response (TLOVR) up to week 48 defined as the first of the two-confirmed HIV-RNA >100 copies/ml (at least two weeks apart);
4. Change in CD4 cell count from baseline to week 48 +/- 21 days;
5. Change in HIV-DNA level from baseline to week 48 +/- 21 days;
6. Change in lipidic profile (total cholesterol, high density lipoprotein-cholesterol, triglycerides, and low density lipoprotein-cholesterol) from baseline to week 48 +/- 21 days;
7. Change in glucose profile from baseline to week 48;
8. Change in Framingham-calculated cardiovascular risk from baseline to week 48;
9. Change in glomerular function rate from baseline to week 48;
10. Proportion of patients with an adverse event throughout week 48;
11. Proportion of patients with a serious adverse event (SAE) throughout week 48;
12. Proportion of patients with a CNS adverse event throughout week 48;
13. Proportion of patients new to DTG with CNS symptoms at 2 and 6 weeks after starting DTG;
14. Change in patients' health-related quality of life from baseline to weeks 12 and 48;
15. Assessment of patient's monitoring satisfaction from baseline to weeks 24 and 48 for patients in the patient-centered monitoring arm;
16. Assessment of the global satisfaction of the monitoring at week 48 for all patients (regardless of the randomisation arm);
17. Proportion of patients in the patient-centered monitoring arm expressing willingness to change monitoring options throughout 48 weeks;
18. Assessment of patient's treatment satisfaction at week 48;
19. Assessment of ARV treatment in the post study;
20. Study satisfaction at week 48;
21. Cost-effectiveness of study arms at 48 weeks;
22. Changes in patient weight from baseline to week 48.

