## 11. STATISTICAL METHODS

### 11.1 Hypotheses

- HA1: DTG + FTC maintenance dual therapy is non-inferior to cART in maintaining plasma HIV viral load <100 copies/ml throughout 48 weeks in virologically suppressed patients.
- HO1 (tested): DTG + FTC maintenance dual therapy is inferior to cART by 12% in maintaining plasma HIV viral load <100 copies/ml throughout 48 weeks in virologically suppressed patients.
- HA2: Patient-centered monitoring reduces health-costs compared to standard monitoring.
- HO2 (tested): Patient-centered monitoring does not reduce health-costs compared to standard monitoring.

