### 11.2 Determination of Sample Size

The first sample size calculation was based on the primary outcome for the comparison between DTG + FTC dual therapy and standard cART, i.e. the comparison between the proportions of patients in the two arms maintaining virologic suppression, using a two-sample proportion test (96). The following assumptions were made:

- Power 80%
- Significance level 0.025 (one-sided Z test of non-inferiority)
- 97% of patients with conventional cART will be virologically suppressed at week 48 (<100 copies/ml)
- 94% of patients on DTG + FTC dual therapy will be virologically suppressed at week 48 (<100 copies/ml)
- Non-inferiority margin of 12% (as in previous non-inferiority trials)(97-104). We chose 12% noninferiority margin because there is no difference in terms of resistance acquisition between 10% and 22% virological failure.

Sample size of 83 patients in each group (total sample size, 166 patients) to achieve 80% power to detect a non-inferiority margin difference between the group proportions of -0.12 was calculated. The power was computed for the case when the actual cART group proportion is 97% and the actual DTG + FTC dual therapy group proportion is 94%. To allow for at least 10% loss to follow-up and also for the randomisation in two steps in this 1:1:1:1 trial, we will aim to recruit **a total of 184 patients**.

The second sample size calculation was based on the primary outcome for the comparison between simplified monitoring and standard monitoring, i.e. the comparison between mean direct costs in the two arms (105). The following assumptions were made:

- Significance level 0.05 (two-sided t-test)
- Direct costs are CHF 25,000 per year (standard deviation (SD) CHF 8,000) with conventional monitoring
- SDs are equal in the two groups (CHF 8,000)

With sample sizes of 92 patients in each group, we will have approximately 55% power to detect a 10% difference in costs, and 99% power to detect a 25% difference in costs. We will also have substantial power to detect small-to-moderate differences in many of the secondary outcomes, e.g. changes in CD4 cell counts or health-related quality of life. The exceptions are rare outcomes such as adverse events, resistance or clinical complications for which the statistical power to detect differences will be low.

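### The primary outcome is sustained suppression over 48 weeks in the objective, outcome, hypothesis and analysis sections, but the synopsis analysis, planning rates and missing-data rule treat it as status at week 48

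*Protocol*

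**What the plan says.** **Sustained suppression.** Section 5.1 gives the outcome as "the proportion of patients maintaining HIV suppression defined as HIV-RNA <100 copies/ml throughout 48 weeks (+/- 21 days", with one blip below 200 copies/ml tolerated if the next value is below 50. The synopsis outcome row agrees: "The first primary outcome will be the maintenance of HIV-RNA <100 copies/ml through the 48-week study duration". Section 11.1 tests non-inferiority "in maintaining plasma HIV viral load <100 copies/ml throughout 48 weeks". The primary objective (4.2) and the primary analysis (11.4.2) are also written for the whole 48-week period.

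**Status at week 48.** The synopsis paragraph on statistical considerations, which carries the estimator, the confidence interval and the decision rule, says "We will evaluate the proportion of patients with viral suppression at week 48 in each arm". Section 11.2 assumes that "97% of patients with conventional cART will be virologically suppressed at week 48 (<100 copies/ml", and 94% on DTG + FTC at the same timepoint. The synopsis assumes 92% in both arms, again at week 48. Section 11.5 replaces a missing final value by the week-36 value and does not mention a failure that came before.

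**What happens to failures.** Under Section 3.7, dual-therapy patients with two consecutive values of at least 100 copies/ml "will be switched to a standard cART regimen while waiting for results of genotypic resistance", and all failing patients complete procedures to week 48. Under Section 11.4.1, ITT analyses everyone in the allocated group, and ITT and per-protocol must reach the same conclusion. That section keeps in the per-protocol set a patient who stopped early, or who lacks a week-48 value, if virological failure came first. The synopsis per-protocol exclusions have no such exception.

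**The concern.** The two wordings are different endpoints for the same patient. Someone on DTG + FTC who fails at week 12, is switched to cART and is suppressed again by week 48 is a failure under Section 5.1 and a success under the synopsis analysis. In ITT the second reading partly measures the regimen that the patient was switched to. It shrinks the difference between arms, and in a non-inferiority trial this favours the conclusion sought.

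The synopsis per-protocol rule adds to this. As written, it drops the same patient for stopping treatment early, so the failure would count as a success in ITT and be absent from per-protocol. The requirement that both analyses agree would then give little protection. The document does not say which text prevails.

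**Working it through.** **1. The plan's own sample size.** Inputs from Section 11.2: 97% and 94%, margin 0.12, one-sided alpha 0.025, power 80%.

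n per arm = (1.960 + 0.842)² × [p_C(1 − p_C) + p_T(1 − p_T)] / [0.12 − (p_C − p_T)]²

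= 7.849 × (0.0291 + 0.0564) / 0.09² = 82.8, so 83. This matches the protocol. Adding 10% gives 83 × 1.1 = 91.3, so 92 per arm and 184 in total. The synopsis rates (92% in both arms) give 7.849 × 0.1472 / 0.12² = 80.2, so 81. The arithmetic is sound. What differs is the label on the rates, and there are two sets of them.

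**2. Size of the bias in ITT under the week-48 wording.** Take true sustained success at the margin: 97% on cART and 85% on DTG + FTC, with 92 per arm. Let r be the fraction of failures in each arm that is suppressed again by week 48. The documents give no value for r, so it is an assumption shown as a range.

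- cART at week 48: 0.97 + 0.03r
- DTG + FTC at week 48: 0.85 + 0.15r
- difference: 0.12 × (1 − r)

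The chance that the lower 95% limit lies above −12% was found in two ways: by the normal approximation Φ[(0.12 − difference)/SE − 1.96], and by simulating 200,000 trials with 46 patients per factorial cell and the Mantel-Haenszel risk difference stratified by monitoring type.

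| r | cART | DTG + FTC | Difference (points) | Normal approx. | Simulation |
|---|---|---|---|---|---|
| 0 | 97.0% | 85.0% | 12 | 2.5% | 3.9% |
| 0.25 | 97.75% | 88.75% | 9 | 13% | 16.8% |
| 0.50 | 98.5% | 92.5% | 6 | 51% | 52.9% |
| 0.75 | 99.25% | 96.25% | 3 | 98% | 94.8% |

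For r = 0.50, for example, SE = √[(0.985 × 0.015 + 0.925 × 0.075)/92] = 0.0302, and 0.06/0.0302 − 1.96 = 0.02, which gives 51%. Starting instead from 92% against 80%, the simulation gives 3%, 12%, 40% and 88%.

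**3. With the Section 11.4.1 safeguard.** If the per-protocol analysis must also show non-inferiority, and earlier failures are kept there as failures, the same simulation gives about 4% at every r.

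**4. TLOVR, a secondary outcome.** Section 5.2 has it "defined as the first of the two-confirmed HIV-RNA >100 copies/ml (at least two weeks apart". The schedule says "Patients with HIV-RNA ≥ 100 copies/ml will benefit from another HIV-RNA measurement after 2 weeks (± 5 days", that is, days 9 to 19. A retest on days 9 to 13 falls short of two weeks, and TLOVR uses a strict inequality where virological failure elsewhere includes a value of exactly 100. A patient can therefore meet the failure definition and be switched without a qualifying TLOVR pair.

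**The case against.** The strongest reply is that the governing sections agree. Objective, outcome, hypothesis and main-text analysis all describe sustained suppression, as does the synopsis outcome row; on the analysis itself, the outlier is one summarising sentence. Under the full text the re-suppressed patient is a failure. This stands, and it limits the point to a contradiction that needs removing. It does not show that the trial will be analysed on the wrong endpoint.

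Second, the ITT figures are not chances of declaring non-inferiority under Section 11.4.1, which also needs per-protocol agreement. Keeping a patient without a week-48 value because failure came first makes sense only if that failure counts. This stands too (step 3), but not under the synopsis exclusions, which lack the exception.

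Third, a reader might infer that the trial was powered for an easier endpoint. The document does not show this. The 83 reproduces, the lead-in to Section 11.2 speaks of maintaining suppression, and no different sustained rate is given. Purely as illustration, if sustained rates were 1, 2, 3 or 5 points lower in both arms, power with 92 per arm would be 76%, 70%, 64% or 55% against 84%; nothing in the protocol says that they are.

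Fourth, not every Section 5.1 failure leads to a switch. A single unconfirmed value of 200 or more fails the definition but triggers none, and failures first seen at week 36 or 48 leave little or no time for re-suppression. So r may be low, and the rescue regimen does not explain every reclassified patient.

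On TLOVR, a reader might take 5 of the 11 permitted retest days (45%) as the share of confirmations lost. It is a count of calendar days; the retest is scheduled for day 14, and the share of early retests is unknown.

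**Conclusion.** The contradiction is in the current text and concerns the primary endpoint. Followed as written, the synopsis analysis would count re-suppressed failures as ITT successes, and the direction of that bias is towards non-inferiority. At the margin, the chance of an ITT non-inferiority result rises from about 4% to 17%, 53% or 95% for re-suppression of 25%, 50% or 75%. This assumes equal fractions in both arms, which the documents do not supply. With the Section 11.4.1 per-protocol requirement, and earlier failures counted as failures, it stays near 4%.

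No error in the sample-size arithmetic is shown. The planning rates need a correct label and one consistent set. The TLOVR mismatch is real but minor and does not touch the primary analysis. The point should be fixed; because the main-text sections already agree, it does not call the design into question.

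**What to change.** 1. Use the Section 5.1 definition in the synopsis statistical considerations, Section 11.2 and Section 11.5.
2. State once, and refer to it in Section 11.5, that a patient who fails to meet Section 5.1 before week 48 remains a failure whatever is measured or carried forward later.
3. Label the planning rates as sustained suppression, with their basis, and reconcile 92%/92% in the synopsis with 97%/94% in Section 11.2.
4. Give the synopsis per-protocol exclusions the Section 11.4.1 exception for patients whose virological failure came first.
5. As a minor item, align the TLOVR definition with the virological-failure definition: two consecutive values of at least 100 copies/ml, with the retest inside its window of 2 weeks ± 5 days.

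The cost is wording in the synopsis and Sections 5.2, 11.2 and 11.5. No visit, measurement or treatment rule changes. If the sponsor judges sustained rates to be below the stated ones, the power statement would be somewhat less favourable.

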#### 11.4.2 Primary analysis

As a first step in this factorial trial, we will test for an interaction between the type of drug treatment and the monitoring type in order to assess if treatment effect is different depending on the type of monitoring. If the test is non-significant we will combine the two types of monitoring for the drug therapy comparison and the two drug therapies for the monitoring comparison. Otherwise, the trial will be analysed as a four-arm trial with a hierarchical testing approach.

For the primary comparison of the primary outcome between the two treatment arms, we will obtain the proportion of patients with viral suppression for 48 weeks in each arm, and compute a Mantel-Haenszel risk difference (DTG+FTC - cART) stratified for the monitoring type with a two-sided 95% confidence interval (107). If the lower confidence limit is higher than -12% we will conclude non-inferiority. If the lower confidence limit is below -12% we will conclude that DTG + FTC is potentially inferior to cART.

For the secondary comparison of the primary outcome between the two monitoring arms, we will calculate a Mantel-Haenszel test statistics and Mantel-Haenszel risk difference (DTG+FTC - cART) stratified for the type of treatment.

Secondary categorical outcomes (proportions of virological suppression <50 copies/mL both as a standard proportion and as FDA snapshot, of loss of future treatment options, of adverse events, of serious adverse events, of CSN adverse events, of CNS symptoms) between the DTG+FTC and cART groups, and between the patient-centered and standard monitoring groups will also be analysed using the Mantel-Haenszel test statistics and Mantel-Haenszel risk difference (DTG+FTC - cART) stratified for the type of monitoring and type of treatment, respectively.

For continuous outcome variables (CD4 count, HIV-DNA level, total cholesterol, high-density lipoproteine, triglycérides, low density lipoprotein-cholesterol, glucose, Framingham-calculated cardiovascular risk, glomerular function rate, weight, health-related quality of life, treatment satisfaction), we will compare the mean values at 48 months between the DTG+FTC and cART treatment groups and between the patient-centered and standard monitoring groups using linear regression adjusted for the type of monitoring and type of treatment, respectively.

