#### 11.4.3 Secondary analysis

For categorical outcomes, we will additionally calculate relative risk differences between groups. We will calculate odds ratios from multiple logistic regression models adjusting for the type of monitoring and type of treatment as appropriate. For repeatedly measured categorical outcome variables (virological suppression <50 copies/mL), we will consider a mixed effects logistic regression with a random intercept on the subject to account for within-patient correlations.

For repeatedly measured continuous outcome variables, we will also consider all measurements in a linear mixed effects regression model to account for within-patient correlations. Finally, we will analyse development over time by exploring the functional relationship between outcome and time using fractional polynomials and a treatment-by-time interaction term.

Moreover, we will evaluate all outcomes in crude analyses not adjusting for type of monitoring or type of treatment. Binary outcomes will be compared by the Chi-squared or Fisher's exact test, continuous outcomes by the Student t-test.

Cost-effectiveness of treatment arms (incremental cost-effectiveness ratio) will be calculated by taking the difference in mean costs between patient-centered arm and standard monitoring arm, and between DTG + FTC dual therapy arm and cART arm, and dividing them by the difference in time to loss of virological response (TLOVR) between the study arms. Difference in TLOVR will be assessed by comparing the area under the patient-centered and standard monitoring Kaplan-Meier curves, and under the DTG+FTC and cART Kaplan-Meier curves. Generalised lo-rank test will be used to compare times between groups.

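### The synopsis tests the first primary outcome at week 48, but Sections 5.1, 11.1 and 11.4.2 define it as suppression throughout 48 weeks; under the synopsis wording a failure re-suppressed on cART counts as a success

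*Protocol*

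**What the plan says.** Four places define the first primary outcome as sustained suppression below 100 copies/ml.

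- Protocol, Study synopsis, outcome row: "The first primary outcome will be the maintenance of HIV-RNA <100 copies/ml through the 48-week study duration".
- Section 5.1: "the proportion of patients maintaining HIV suppression defined as HIV-RNA <100 copies/ml throughout 48 weeks", with an allowance for a single blip during the study, which only makes sense for a sustained outcome.
- Section 11.1: both hypotheses are framed on maintaining suppression throughout 48 weeks.
- Section 11.4.2: "we will obtain the proportion of patients with viral suppression for 48 weeks in each arm".

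Two places use status at one time point.

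- Study synopsis, Statistical Considerations: "We will evaluate the proportion of patients with viral suppression at week 48 in each arm". The estimator, confidence interval, margin and analysis sets follow, so this is a full decision rule.
- Section 11.2: "97% of patients with conventional cART will be virologically suppressed at week 48 (<100 copies/ml"), with the matching 94% for dual therapy. The same section names the outcome being sized as the proportion maintaining suppression.

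Three further rules decide what the difference does.

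- After failure (Section 3.7), dual-therapy patients "will be switched to a standard cART regimen while waiting for results of genotypic resistance" and complete procedures to week 48. ITT keeps everyone in the allocated group.
- Per protocol: Section 11.4.1 excludes early stoppers unless virological failure came first. The synopsis rule excludes them with death as the only exception.
- Missing data: Section 11.5 carries the week-36 value forward to the final time point and does not mention an earlier failure.

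**The concern.** If failures had no route back to suppression, the two wordings would differ little. Here the protocol provides one. A dual-therapy patient who fails, switches to cART and is suppressed at week 48 is a failure under Section 5.1 and an ITT success under the synopsis analysis. The success is then achieved on the comparator strategy but credited to dual therapy. In a non-inferiority trial this moves the estimated difference towards zero and so towards the claim.

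The trial is open-label and, by Section 11.3, HIV-RNA results reach investigators within a week. Two versions of the primary rule leave room to choose between them once results are known.

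**Working it through.** **1. The plan's own sample size.** Inputs from Section 11.2: 97% v 94%, margin 12%, one-sided 0.025, power 80%.

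n = (1.960 + 0.8416)² × (0.97×0.03 + 0.94×0.06) / (0.12 − 0.03)² = 7.849 × 0.0855 / 0.0081 = 82.8, so 83 per group. This reproduces. 83 × 1.10 = 91.3, giving the stated 92. The arithmetic is not in question.

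**2. One patient under each text.** Dual therapy; confirmed failure around week 12; switched to cART; below 100 copies/ml at weeks 36 and 48.

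| Text | Result |
|---|---|
| 5.1, 11.1, 11.4.2 | failure |
| Synopsis analysis, ITT | success |
| 11.4.1 per protocol | kept, because failure came first |
| Synopsis per protocol | excluded, having stopped the allocated treatment |
| 11.5, if week 48 is missing | week-36 value carried forward: suppressed |

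Change of therapy is listed as a failure in Section 9.2.2, but only for the secondary snapshot outcome.

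**3. One illustrative dataset** (crude Wald limit, 92 per arm).

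- Sustained: cART 89/92 = 0.967, dual therapy 80/92 = 0.870. Difference −0.098; SE = √[(0.967×0.033 + 0.870×0.130)/92] = 0.0397; lower limit −0.098 − 1.96×0.0397 = −17.6%. Non-inferiority not shown.
- Five of the 12 dual-therapy failures re-suppressed: 85/92 = 0.924. Difference −0.043; SE 0.0333; lower limit −10.9%. Non-inferiority declared.
- With a Miettinen-Nurminen score limit (the difference D at which (p_T − p_C − D)/SE(D) = 1.96, SE(D) from the rates fitted under D), five gives −12.1%, just short, and six (86/92) gives −10.7%.

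**4. Chance of declaring non-inferiority.** Assume true sustained rates exactly at the margin, 97% v 85%, 92 per arm, and a share r of failures re-suppressed by week 48 in both arms. The week-48 rate is p + r(1 − p); for r = 0.5 this is 0.97 + 0.5×0.03 = 98.5% and 0.85 + 0.5×0.15 = 92.5%. Exact binomial enumeration, ignoring the monitoring stratum:

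| r | Rates (cART v dual) | Score limit | Crude Wald limit |
|---|---|---|---|
| 0 (sustained outcome) | 97.0% v 85.0% | 2% | 4% |
| 25% | 97.75% v 88.75% | 9% | 17% |
| 50% | 98.5% v 92.5% | 34% | 53% |
| 70% | 99.1% v 95.5% | 72% | 89% |

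**5. Sizing, if the 97% and 94% are week-48 rates.** The protocol gives no separate sustained rates, so assume both arms have extra failures, keeping the 3-point gap. Power = Φ{(0.12 − 0.03)/SE − 1.96}, with SE = √{[p_C(1−p_C) + p_T(1−p_T)]/n}.

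| Extra failures per arm | 83 per arm | 92 per arm |
|---|---|---|
| 0 points (97/94) | 80% | 84% |
| 1 point (96/93) | 72% | 77% |
| 2 points (95/92) | 65% | 70% |
| 4 points (93/90) | 55% | 59% |

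**The case against.** The best defence is that the body of the protocol is consistent. Every section that defines the outcome, states the hypothesis or specifies the analysis says sustained suppression, and the week-48 analysis sentence stands in a condensed synopsis box. Section 11.4.1 keeps a failed patient who has no week-48 result, which makes sense only if the earlier failure already decides the outcome. It also requires the per-protocol and ITT analyses to agree. This stands, and it limits the point to a conflict of text.

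It does not remove the conflict. The synopsis contradicts its own outcome row and states a complete decision rule. The imputation rule in Section 11.5, in the body, is also written around one final time point.

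Three stronger readings might be inferred, and the documents do not support them.

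- *Early failures vanish from both analysis sets.* This needs the synopsis per-protocol rule. Section 11.4.1 contradicts it by keeping patients with earlier virological failure.
- *The trial was sized on an easier outcome.* Section 11.2 also speaks of maintaining suppression, so its week-48 label may be shorthand. The label is ambiguous; an error is not shown.
- *The visit-level model in Section 11.4.3 has the same fault.* There the team says "we will consider a mixed effects logistic regression with a random intercept on the subject", for a secondary outcome below 50 copies/ml. Describing status at each visit in the allocated group is legitimate.

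The magnitudes also have limits. The re-suppression shares have no source in the protocol. Equal shares in both arms are a simplification, since Section 3.7 has cART failures wait for the genotype while dual-therapy failures switch at once. Neither limit computed is the stratified Mantel-Haenszel interval that Section 11.4.2 cites.

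**Conclusion.** The point holds as a contradiction in the stated primary decision rule. Read alone, the definition in Section 5.1 is sound; the bias arises only if the synopsis wording is applied. If it is, a handful of re-suppressed failures can reverse the conclusion: five in the worked dataset with a crude Wald limit, six with a score limit. At the margin, the chance of a false claim rises from 2-4% to 9-17%, 34-53% or 72-89% for assumed re-suppression of 25%, 50% or 70%. The direction follows from the protocol's own procedures; the size depends on those assumptions.

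For the sample size, the finding is only that the outcome behind the 97% and 94% is unclear. The synopsis also gives a different planning rate (92% in both arms), which is a separate matter.

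**What to change.** - In the synopsis Statistical Considerations, replace week-48 status with the Section 5.1 definition.
- Align the synopsis per-protocol rule with Section 11.4.1, including its exception for earlier virological failure.
- State in Section 11.4.2 and again in Section 11.5 that a patient who has met failure under Section 5.1 stays a failure, whatever later or carried-forward values show.
- In Section 11.2, say whether 97% and 94% are rates for the sustained outcome. If they are week-48 rates, restate power for the sustained outcome, with a range such as that in step 5.
- Keep week-48 status as the secondary snapshot outcome, and leave the Section 11.4.3 model as it is.

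The cost is wording in the synopsis and Sections 11.2, 11.4.2 and 11.5. No new data are needed and patient management does not change. The one downside is that the stated power may become less favourable.
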